#### Dose-expansion part

2.7.2

After the dose-escalation part has been terminated, additional patients are treated until a total of 20 patients have received the DL defined as the MTD. During the dose-expansion part, patients can be treated simultaneously. Prior to the start of the dose-expansion part, a substantial amendment including the applied DLs will be submitted to the regulatory authorities.

### Endpoints of the study

2.8

The primary endpoints of the dose-escalation part are incidence and severity of AEs, including AESIs, serious AEs (SAEs) and suspected unexpected serious adverse reaction (SUSARs) [CTCAE v5.0 and for CRS modified criteria by Lee et al. (36)], from first application of CC-3 at week 1 until week 4 or, in case of early termination, last assessment. The primary endpoints of the dose-escalation and dose-expansion parts are the best objective response, defined as stable disease (SD), partial remission (PR), or complete remission (CR) until end of study (EOS) compared to baseline based on routine imaging according to RECIST 1.1.

Secondary endpoints include general long-term safety, product-specific safety aspects, clinical efficacy endpoints, and pharmacokinetics:

• Safety (general): incidence and severity of AEs including AEs of special interest (AESIs), SAEs, and SUSARs according to CTCAE v5.0 from first application of CC-3 until EOS visit or, in case of early termination, last assessment• Efficacy:  ○ Objective tumor response assessed by RECIST 1.1 on routine imaging at week 8, week 16, and at EOS visit;  ○ Disease control rate (CR, PR, and SD) at each visit until end of the clinical trial.• Survival:  ○ OS defined as the time from first administration of CC-3 to time of death from any cause. Patients without the event are censored on the last date of follow-up;  ○ Progression-free survival defined as the time from first administration of CC-3 to progression of disease or death from any cause, whichever occurs first. Patients without the event are censored on the last date of follow-up.• Pharmacokinetics: CC-3 serum concentrations assessed at week 1, week 2, and, in case of second priming dose, at week 3• Quality of life: overall quality-of-life scores (EORTC QLQ C-30) at screening visit, week 5, week 9, week 13, end of treatment (EOT) visit, follow-up (FU) visit, and EOS visit.

Exploratory endpoints include an analysis of PDK and cytokine levels in serum, changes from baseline in the tumor-markers CEA and CA 19-9, as well as a correlation of the effect of CC-3 on serum cytokine levels and PDK biomarkers and a correlation of safety and efficacy of CC-3 treatment with clinical, biological, and patient characteristics. An analysis of CD276 expression is not deemed necessary at the time of enrolment, as an expression of CD276 was shown on all CRC tumor samples analyzed in preliminary assessments. However, if tumor samples are available, then CD276 expression will be evaluated. The rate of patients undergoing secondary resection of liver metastases after initially irresectable disease until EOS will also be assessed.

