**Figure 2 f2:**
[figure not shown]
Dose-escalation part. **(A)** Dosing. First patient (Pat 1) receives 50 µg weekly over 16 weeks. During 3 weeks after first application, dose-limiting toxicity (DLT) will be evaluated and the dose level (DL) for the next patient (Pat 2) will be determined by safety review committee (SRC). Repetition of SRC-guided accelerated dose escalation with following patients until occurrence of DLT, AEs ≥2, or decision of SRC, in patient X (Pat X). Switch to 3 + 3 design with last DL before reaching a criterion (Pat X-1) being used as a priming dose (green frame) for the first application, followed by the DL at which the stopping criterion was observed (Pat X) in subsequent applications. When last patient of each cohort has been observed for 21 days after application of target dose, DLT will be evaluated and the dose level for next cohort of at least three patients is determined by SRC. * up to two additional subjects may be enrolled at each DL; ** up to six additional subjects may be enrolled at each DL; *** SRC may decide to add one additional priming dose, so that target dose is reached at week 3 and DLT evaluation period thus prolonged until end of week 4 (dashed lines). **(B)** Flowchart. If no DLT, AEs grade ≥2, or respective decision of SRC occurs, dose levels may be incremented by up to 100% during accelerated dose titration, enabling a rapid increase up to the maximum target dose after a potential minimum of eight patients. After switching to 3 + 3 design, the number of patients per cohort depends on occurrence of DLT, until maximum tolerated dose (MTD) is reached.

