### Treatment/study distribution

2.7

The study will be divided into two parts. In both, patients receive CC-3 monotherapy as short-term infusion over 3 h once per week, with up to 16 applications per patient if no criterion for treatment termination is met (see treatment schedule in **Figure 3**). Depending on the tolerability of the first three doses, which are always applied in the inpatient setting, further applications may be applied in an outpatient setting at the investigator’s discretion. The treatment phase is followed by a treatment free period of 8 weeks with weekly follow-up visits; the end of safety follow-up visit is thus scheduled for week 24. The duration of the trial for each patient is expected to be 6 months. Thereafter, patients will receive routine treatment by the admitting oncology center. Long-term follow-up data will be collected by telephone calls outside the clinical trial protocol for 3 years. In case of a confirmed benefit of the CC-3 treatment within the clinical trial, a continuation of CC-3 treatment outside the study is possible. A possible continuation will be based on a case-by-case decision by the investigator and the SRC.

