#### Dose-escalation part

2.7.1

Initially, dose escalation will be conducted using an accelerated titration design with single-patient cohorts for each DL. Up to two additional subjects may be enrolled at each DL in case more PK, pharmacodynamic (PDK), or safety data are deemed necessary by the SRC. A staggered enrollment design is used for each DL, with a minimum observation period of 72 h between two consecutive subjects’ first doses with the same DL. This is considered sufficient to identify CRS as most critical toxicity. Every patient receives a fixed dose, starting with 50 µg in the first cohort. Subsequent doses are determined by the SRC based on PK, PDK, and safety data obtained with the last DL over an observation period of 21 days, during which DLT evaluation is conducted. This accelerated phase will be replaced by a standard 3 + 3 design in case of

any AE grade ≥2 (except AEs unequivocally due to underlying disease or an extraneous cause);occurrence of DLT;DL ≥800 µg; anddecision of SRC based on PK, PDK, and safety data.

In the standard titration phase of the dose-escalation part, the last DL safely applied prior to termination of the accelerated phase is used as priming dose upon first application, followed by the DL at which the stopping criterion was observed in week two and thereafter. Based on PK, PDK, and safety data, the SRC may decide to introduce an additional intermittent priming dose at week 2, in which case the target dose will be applied at week 3. At least three patients are treated per cohort, following a rule-based 3 + 3 design. Up to a maximum of nine patients per cohort may be enrolled if more PK, PDK, or safety data are deemed necessary by the SRC. After completion of the first cohort’s DLT evaluation period (21 days after application of the target dose to the last patient), the DL for the next cohort will be determined by the SRC. This will be done considering all AEs and DLTs as well as PK, PDK, and safety data. The DL can be increased up to 100% of the previous dose. The priming dose applied in the first cohort will further be given at week 1 of every consecutive cohort, followed by the target dose at week 2 or 3, depending on whether the SRC deemed an intermittent priming dose necessary at week 2 (**Figure 2A**).

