### Safety/dose-limiting toxicity

2.9

Toxicity will be graded according to the National Cancer Institute CTCAE (v5.0) and the CRS grading system by Lee et al. (36). All AEs and SAEs will be documented and reported according to good clinical practice guidelines. Furthermore, we will report on AESIs, which include occurrence of CRS, infusion-related reactions upon study drug administration and drug induced liver injury (DILI). These AESIs will be monitored closely and included in patient safety narrative reports to the data safety monitoring board (DSMB).

DLT is defined as any AE grade ≥3 that the investigator considers to be at least possibly related to study treatment and occurring within the DLT safety period (from first study drug treatment to day 21 or 28, respectively, if an additional intermittent priming dose is given) with few exceptions. Notably, grade ≥3 CRS lasting less than 48 h, grade ≥3 nausea, vomiting or diarrhea in patients who have not received optimal antiemetic or antidiarrheic treatment, as well as isolated ≥3 laboratory abnormalities resolving within 7 days and without clinical sequelae are not considered a DLT. Likewise, liver toxicity caused by obstruction, metastasis, or infection; grade ≥3 transaminitis or direct hyperbilirubinemia for <4 days; grade 3 fatigue for ≤5 days; grade 3 infusion reaction resolving within 8 h; nor grade 3 but adjustable (i.e., not refractory) arterial hypertension are not considered a DLT.

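### The primary adverse-event window is fixed at week 1 to week 4 whatever week the tested dose starts, so incidence is not comparable across differently primed dose levels

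*Protocol article*

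**What the plan says.** Section 2.8 of the protocol article gives the dose-escalation part one primary safety endpoint: incidence and severity of AEs "from first application of CC-3 at week 1 until week 4 or, in case of early termination, last assessment". The same window applies to every escalation patient.

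The start of the dose level under test varies. Infusions are given "once per week, with up to 16 applications per patient" (section 2.7). In the accelerated phase the first infusion is already the tested level: "Every patient receives a fixed dose, starting with 50 µg in the first cohort" (section 2.7.1). In the 3+3 phase a priming dose comes first, "followed by the DL at which the stopping criterion was observed in week two and thereafter". The safety review committee may add a second priming dose in week 2, "in which case the target dose will be applied at week 3".

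Other windows in the article do respond to that second priming dose. The pharmacokinetic endpoint in section 2.8 gains a week-3 assessment. The DLT period in section 2.9 runs "from first study drug treatment to day 21 or 28, respectively, if an additional intermittent priming dose is given", and the Figure 2 legend says that the "target dose is reached at week 3 and DLT evaluation period thus prolonged until end of week 4". The primary AE window is not adjusted.

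The DLT period is also described in another way. Section 2.7.1 closes it "21 days after application of the target dose to the last patient", and section 2.10 and another sentence of the Figure 2 legend likewise count 21 days from the target dose.

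**The concern.** The window is anchored on the first infusion of any dose, while the level being tested may start one or two weeks later. The time observed at the tested level therefore depends on how many priming doses came before it, and the rest of the window is spent at a lower dose. The unprimed patients are at the lowest levels and the primed cohorts are at the higher ones, so observation time is tied to dose. In Table 1 the 113 µg level occurs in both phases, so one nominal level would be observed for two different lengths of time.

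At stake is whether the primary AE incidence can be read across dose levels, and whether it captures events that the plan's own 21-day period after the target dose is meant to catch.

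**Working it through.** **Inputs.** Weekly dosing (section 2.7). Tested level starts in week 1, 2 or 3 (section 2.7.1, Figures 2 and 3). With the first infusion on day 1, the start days are 1, 8 and 15. The article does not say whether the window closes at the end of week 4 (day 28) or at its start (21 completed days), so both are shown.

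**Target-dose days** = last day of window − start day + 1.

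| Schedule | Start day | To day 28 | Tested-level infusions in weeks 1–4 | To start of week 4 | Last day of a 21-day target-dose period |
|---|---|---|---|---|---|
| No priming | 1 | 28 | 4 | 21 | 21 |
| One priming dose | 8 | 21 | 3 | 14 | 28 |
| Two priming doses | 15 | 14 | 2 | 7 | 35 |

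**Against the plan's own 21 days.** On the day-28 reading, one priming dose gives 28 − 8 + 1 = 21 days, which matches. Two priming doses give 28 − 15 + 1 = 14 days, which is 7 short: days 29 to 35 lie outside the primary endpoint. On the start-of-week-4 reading, one priming dose also falls short (14 days).

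**The DLT periods disagree among themselves.** Counting from first treatment as in section 2.9, one priming dose gives 21 − 8 + 1 = 14 target-dose days and two give 28 − 15 + 1 = 14. Sections 2.7.1 and 2.10 give 21. The Figure 2 legend contains both versions. A DLT in days 29 to 35 is possible only on the 21-days-after-target version.

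**Ratios, day-28 reading.** One priming dose against none: 21/28 = 75%. Two against none: 14/28 = 50%. Two against one: 14/21 = 67%. On the other reading, two against none is 7/21 = 33%.

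**Effect on observed incidence.** The article gives no AE rates, so these are assumptions.

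*Constant hazard at the tested level, negligible AEs from priming, day-28 reading.* Incidence over d days = 1 − (1 − I)^(d/28), where I is the 28-day incidence.

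| I | No priming | One priming dose | Two priming doses |
|---|---|---|---|
| 30% | 30.0% | 23.5% | 16.3% |
| 40% | 40.0% | 31.8% | 22.5% |
| 50% | 50.0% | 40.5% | 29.3% |

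For 40%: 1 − 0.6^0.75 = 31.8% and 1 − 0.6^0.5 = 22.5%. The relative shortfall is about 20% with one priming dose and 41% to 46% with two. A lower rate brings it closer to half: at 5% per week, 4 weeks give 1 − 0.95^4 = 18.5% and 2 weeks give 1 − 0.95^2 = 9.8%, a shortfall of 47%.

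*Risk falling over time.* Take 20% in the first target-dose week, multiplied by a factor f each week after.

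| f | 4 weeks | 3 weeks | 2 weeks | Two priming doses ÷ none |
|---|---|---|---|---|
| 1 | 59.0% | 48.8% | 36.0% | 0.61 |
| 0.5 | 33.3% | 31.6% | 28.0% | 0.84 |
| 0.25 | 25.2% | 24.9% | 24.0% | 0.95 |
| 0 | 20.0% | 20.0% | 20.0% | 1.00 |

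The understatement therefore depends on when AEs occur and vanishes if all of them arise in the first target-dose week.

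**The case against.** A common window from first dose is a defensible choice for a step-up regimen, because priming is part of the treatment and total observation is then equal. Section 2.8 does not say that the endpoint compares dose levels, and tabulation by level or by onset may be in an analysis plan that is not shown. Every 3+3 cohort receives a week-1 priming dose, so those with one priming dose have the same target-dose time as each other. The factor of one half needs the optional second priming dose and a comparison with unprimed single-patient cohorts, which supply only 3 of 63 patients in Table 1 and 4 of 19 in Table 2. AEs to the end of study (week 24) are a secondary endpoint, and planned target infusions there are 16, 15 or 14, a small difference. Extending only the end date would also create unequal total windows, for example 28, 35 and 42 days.

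Most of this stands. It limits the size of the problem and it shapes the remedy. It does not explain why the pharmacokinetic and DLT windows respond to a second priming dose while the primary AE window does not, and the window itself is fixed in section 2.8, not left open.

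Two stronger readings are tempting. The first is that primed levels look less toxic than they are. The article does not support this as a fact: AEs from priming also count, and the article considers a 72-hour stagger sufficient to identify cytokine release syndrome, which it calls the most critical toxicity, so early onset is plausible. That figure justifies staggering, however. The plan still evaluates DLTs over 21 days or more and lists drug-induced liver injury among its events of special interest, so later events cannot be dismissed. The second is that dose selection is biased. The MTD rests on the DLT count and the next level on all AEs, DLTs, pharmacokinetic and pharmacodynamic data (sections 2.7.1 and 2.10), so no decision is shown to depend on the week 1–4 incidence.

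**Conclusion.** The point holds as a defect of comparability and coverage in the reported primary safety endpoint. On the day-28 reading the endpoint covers 28, 21 or 14 days at the tested level. Cohorts with one priming dose keep the plan's 21 days; cohorts with two lose about a week of it.

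The understatement of AE incidence on that reading ranges from none to nearly half. The upper end needs constant hazard, negligible AEs from priming, and two priming doses compared with none. If the window closes at the start of week 4, every schedule loses a further week. The documents do not establish that toxicity will be understated, or that the MTD or escalation will be affected. It is worth correcting because the endpoint is primary and the correction is cheap.

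**What to change.** In section 2.8, define the by-level primary AE summary over the same number of days after the first administration of the tested dose level in all patients. The 21 days that the plan already uses after the target dose would be one choice; the summary would then end on day 21, 28 or 35. Tabulate AEs with onset during priming separately, under the priming dose. Both parts are needed, because moving the end date alone makes total windows unequal. State whether week 4 means its start or its end if that wording is kept.

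Reconcile this window with the DLT periods in sections 2.7.1, 2.9 and 2.10 and the Figure 2 legend, which do not agree with one another.

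The cost is endpoint and analysis wording. AEs are already recorded to the end of study, so no dosing, visit or data change is needed. With 21 days, the summary ends about a week later than day 28 for patients with two priming doses, and slightly more of them may leave before it closes. For unprimed patients it ends a week earlier than day 28, and those later events remain in the secondary safety endpoint.

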### Sample size calculation

2.11

The total sample size of the trial is assumed to be approximately 77 patients but depends on the observed safety profile, the number of dose cohorts evaluated, and the number of patients per cohort in the dose-escalation part and can therefore vary. Assuming a dose increase of 50% between cohorts, one treated patient per cohort in the accelerated phase (in total three cohorts), six treated patients per cohort (in total 10 cohorts) in the standard titration phase, a starting dose of 50 µg and a tested dose of 4,000 µg, and the estimated number of patients in the dose-escalation part is 63. In the dose-expansion part, up to 20 patients will be treated with the MTD. In this way, we will be able to estimate within a single-stage phase II design an objective response. For this purpose, objective response will be defined as SD, PR, or CR estimating P0 as the maximum response proportion of a poor drug of ≤20% of the patients and P1 as the minimum response proportion of a good drug of ≥50% with a power of 80% and a type one error of 5%. To this aim, we will need n = 17 evaluable patients assuming a dropout rate of 15% (n = 3).

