In addition, the implemented one-patient-cohort escalation of CC-3 in the accelerated titration part is considered to benefit the patients included in this trial. Usually, the focus of phase I clinical trials is primarily set on safety and tolerability, and patients enrolled during early phases of a trial frequently do not receive sufficiently effective doses. This problem is addressed in our trial by our approach to rapidly increase CC-3 DLs in order to reach preclinically effective doses already in patients included early in the study. If no DLT is observed, then DL may be increased by up to 100% from one patient to the next, enabling an exponential dosage increment allowing to reach the maximum dose of 4,000 µg already with the 14th patient in case no DLT occur. A dose expansion part will then follow the dose-escalation part to collect first signs of efficacy and define the RP2D.

With the CC-3 antibody showing convincing preclinical activity, we expect that the study will demonstrate a corresponding clinical efficacy regarding objective tumor response and disease control rate, leading to a due benefit for this particular patient population through a trial that is fully funded by public resources.

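### The primary endpoint tested at 20% versus 50% is called objective response but counts stable disease, so it is best-status disease control and should be named so

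*Protocol article*

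**What the plan says.** **Section 2.8, primary endpoint.** For the dose-escalation and dose-expansion parts the article names "the best objective response, defined as stable disease (SD), partial remission (PR), or complete remission (CR) until end of study (EOS"), compared with baseline on routine imaging by RECIST 1.1.

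**Section 2.11, hypothesis.** The definition is repeated: "objective response will be defined as SD, PR, or CR". The test sets P0 at no more than 20% for a poor drug and "P1 as the minimum response proportion of a good drug of ≥50"%, with 80% power and 5% type I error. This gives 17 evaluable patients, or 20 with 15% dropout.

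**Section 2.8, secondary endpoints.** Two are relevant: "Objective tumor response assessed by RECIST 1.1 on routine imaging at week 8, week 16, and at EOS visit", with no response categories given, and "Disease control rate (CR, PR, and SD) at each visit until end of the clinical trial".

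**Abstract.** The primary efficacy endpoint is described as best objective response by RECIST 1.1. Stable disease is not mentioned.

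**Section 3, Discussion.** The authors expect the study to show "clinical efficacy regarding objective tumor response and disease control rate", which names two different things.

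**The concern.** The tested primary and the secondary disease control rate are built from the same three categories, yet only the primary is called objective response. Someone who reads the Abstract, or a results report that uses the primary's name, will take it to mean tumour shrinkage to at least partial remission. Under the definition in Sections 2.8 and 2.11, the test can succeed with no such patient.

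The secondary objective tumour response does not resolve this. Its categories are not stated, so it may or may not include stable disease.

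What is at stake is the meaning of the efficacy result. A disease control finding would be published as an objective response finding, and could be set beside CR plus PR rates with which it is not comparable.

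**Working it through.** **1. Inputs (Section 2.11).** P0 = 0.20, P1 = 0.50, type I error 0.05, power 0.80, 17 evaluable patients, 15% dropout. Sidedness and cut-off are not stated.

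**2. Reproducing n = 17.** Let X be the number of evaluable patients with best status SD, PR or CR, so X ~ Binomial(n, p). For each n, take the smallest cut-off r with P(X ≥ r | p = 0.20) ≤ 0.05, then compute P(X ≥ r | p = 0.50).

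| n | r | alpha at 0.20 | power at 0.50 |
|---|---|---|---|
| 14 | 6 | 0.0439 | 0.788 |
| 15 | 7 | 0.0181 | 0.696 |
| 16 | 7 | 0.0267 | 0.773 |
| 17 | 7 | 0.0377 | 0.834 |

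The smallest n with power of at least 0.80 is 17, with success at 7 or more. A cut-off of 6 would be too low: P(X = 6 | 0.20) = 12376 × 0.2⁶ × 0.8¹¹ = 0.068, which takes the tail to 0.0377 + 0.068 = 0.106. Dropout: 17 / (1 − 0.15) = 20. Both of the article's figures are reproduced.

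**3. Dependence on sidedness.** A two-sided normal approximation also gives 17: ((1.96 × √0.16 + 0.842 × √0.25) / 0.30)² = 16.1, rounded up. An exact test at 0.025 per side would need 19 (cut-off 8, alpha 0.023, power 0.820). If 8 of 17 were required, alpha would be 0.011 and power 0.685. Whatever the cut-off, stable disease counts towards it.

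**4. Success on stable disease alone.** Seven SD with no CR and no PR gives X = 7, so the rule is met with an observed rate of 7/17 = 41%. If the true rates were SD 50% and CR plus PR 0%, the success probability would be the full design power, 0.834. If the composite stays at 50% and the true CR plus PR rate is *o*, the probability of success with no CR or PR observed is

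Σ (x = 7 to 17) C(17, x) (0.50 − *o*)ˣ 0.50¹⁷⁻ˣ,

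which is 0.58 for *o* = 2% and 0.32 for *o* = 5%. These values of *o* are assumptions for illustration; the article gives none.

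**5. The same data, named both ways.** Under the present label: objective response in 7 of 17 (41%), null rejected. As CR plus PR: 0 of 17, with exact 95% upper limit 1 − 0.025^(1/17) = 0.195, so 0% to 19.5%.

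**6. The two endpoints side by side.**

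| | Primary | Secondary disease control rate |
|---|---|---|
| Categories | SD, PR, CR | CR, PR, SD |
| Time frame | best status until end of study | each visit |

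Section 2.7 has weekly treatment and weekly follow-up visits, while the response endpoint next to disease control names imaging at week 8, week 16 and end of study. On that schedule, most visits have no scan from which disease control could be read.

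**The case against.** The strongest defence is that nothing is hidden. Sections 2.8 and 2.11 both say that stable disease counts, the 20% and 50% rates are set for that composite, and n is correct for it. Endpoint, hypothesis and sample size agree with each other. This stands, and it limits the point to the name and to what may be claimed under it.

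Other parts of the defence also hold:

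- The primary and the secondary disease control rate are not one identical quantity. Their time frames differ.
- The Discussion need not contradict the primary, because its two terms match the names of the two secondary efficacy endpoints.
- A separate response endpoint does exist. It lacks only its categories.

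Several stronger readings are tempting, and the documents do not support them:

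- *The 5% error is not held.* A reader might argue that background disease control exceeds 20%. The article gives no background rate, and a condensed article may leave the justification of P0 to the full protocol. That would also be a dispute about P0, which renaming the endpoint would not settle. At the stated P0 the derived alpha is 0.038, within plan.
- *Stable disease lacks a minimum duration or a rule for new anticancer therapy.* Such rules are commonly left to the full protocol or analysis plan. The first response scan named is already at week 8.
- *The phase II trial would be planned on this test.* Section 2.2 ties phase II to the maximum tolerated dose and the recommended dose and describes efficacy in the expansion part as first evidence. Nothing makes this test a go/no-go gate.

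What the defence does not remove is the Abstract's silence on stable disease, the undefined secondary response endpoint, and a primary name that promises more than the test can show.

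**Conclusion.** The point holds as a fault of naming and definition and should be fixed. The tested primary is disease control, measured as best status until end of study, under the name objective response. Under the derived rule of 7 of 17, seven patients with stable disease and no remission would count as a positive objective response result; the CR plus PR rate in the same data would be 0% with an exact 95% upper limit of 19.5%.

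This rests on the one-sided exact design that reproduces n = 17. Another cut-off would change the number of stable patients needed but not the conclusion. The type I error, the power and the sample size for the composite are not in question.

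**What to change.** 1. In the Abstract, Section 2.8 and Section 2.11, name the tested endpoint *disease control (best response CR, PR or SD until end of study)*, and describe P0 and P1 as disease control proportions. Keep the 20% versus 50% test and n = 17.
2. In Section 2.8, define the secondary objective tumour response as CR plus PR, report it with an exact 95% confidence interval, and word any claim about tumour response on that basis.
3. In Section 2.8, tie the secondary disease control rate to the week 8, week 16 and end-of-study imaging in place of every visit.

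The cost is wording only, with no added patients, visits or scans. The drawback is a primary claim that sounds less favourable. Keeping the present name and restricting the primary to CR plus PR would cost more: it needs its own P0 and P1, which the article does not give. For assumed pairs from 5% versus 30% to 5% versus 20%, the same exact one-sided method gives 14 to 27 evaluable patients.

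### PFS is censored at last follow-up, as OS is, rather than at the last tumour assessment, so patients in contact but no longer scanned push PFS upward

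*Protocol article*

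**What the plan says.** Section 2.8 (Endpoints of the study) defines the endpoint as "Progression-free survival defined as the time from first administration of CC-3 to progression of disease or death from any cause, whichever occurs first". The censoring rule follows directly: "whichever occurs first. Patients without the event are censored on the last date of follow-up". The OS bullet just before it uses the same sentence: "time of death from any cause. Patients without the event are censored on the last date of follow-up".

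The imaging schedule is in the same section: "Objective tumor response assessed by RECIST 1.1 on routine imaging at week 8, week 16, and at EOS visit".

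Contact is more frequent than imaging. Under section 2.7 (Treatment/study distribution), CC-3 is given weekly for up to 16 applications. Then "The treatment phase is followed by a treatment free period of 8 weeks with weekly follow-up visits", and "the end of safety follow-up visit is thus scheduled for week 24". After that, "Long-term follow-up data will be collected by telephone calls outside the clinical trial protocol for 3 years".

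The article does not say that follow-up in the PFS rule means radiological follow-up, and it does not say whether the telephone calls set the last date of follow-up. For safety data after early termination, section 2.8 does refer to the last assessment; the PFS rule does not.

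**The concern.** Death can be established at any visit or call, so last contact is a sound censoring date for OS. RECIST progression needs an image. If a patient's last scan shows no progression and the patient is then seen weekly without another scan, the stated rule keeps that patient in the Kaplan-Meier risk set as progression-free while progression is not being assessed. Any progression in that interval goes unrecorded, and the error runs in one direction: PFS looks longer than it is.

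At stake is a secondary efficacy estimate from a trial that section 2.2 describes as collecting first evidence for efficacy. Because the article fixes the rule, an analysis plan that censored at the last assessment would contradict it, and one that followed it would carry the bias.

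**Working it through.** The article gives no PFS median, rate, event count or power, so there is no stated figure to reproduce. The check is an illustration on assumed inputs.

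**From the article:** scans at weeks 8, 16 and end of study (read here as week 24); weekly contact to week 24; death counts as a PFS event.

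**Assumed:** exponential PFS with a 12-week median; 15% or 30% of patients progression-free at week 8 have no later scan but stay in contact to week 24; OS medians of 4 to 12 months where deaths are allowed.

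**Step 1, true values.**
- PFS at week 8: 0.5^(8/12) = 0.630.
- PFS at week 24 given progression-free at week 8: 0.5^(16/12) = 0.397.
- True week-24 PFS: 0.630 × 0.397 = 0.25.

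**Step 2, stated rule, no deaths among unscanned patients (upper end).** With unscanned share u, estimated week-24 PFS = 0.630 × [(1 − u) × 0.397 + u].
- u = 0.15: 0.630 × (0.337 + 0.15) = 0.307.
- u = 0.30: 0.630 × (0.278 + 0.30) = 0.364.

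**Step 3, stated rule, deaths allowed (lower end).** Replace u by u × s, where s is survival over the 16 weeks (3.68 months) from week 8 to week 24. For an OS median of 4 months, s = 0.5^(3.68/4) = 0.528; for 12 months, s = 0.5^(3.68/12) = 0.808.
- u = 0.15: 0.630 × (0.337 + 0.079) = 0.262, to 0.630 × (0.337 + 0.121) = 0.289.
- u = 0.30: 0.630 × (0.278 + 0.159) = 0.275, to 0.630 × (0.278 + 0.243) = 0.328.

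Patients progression-free at week 8 may die more slowly than these OS medians imply, so step 3 is a lower-end illustration. Steps 2 and 3 together give about 26% to 36% against 25%.

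**Step 4, censoring at the last scan.** If scans stop at random, unscanned patients leave the risk set at week 8 and the rest give 0.630 × 0.397 = 0.25, the true value. Now suppose that, after week 8, scans stop in 40% of those who progress by week 24 and in 10% of the others (assumed, no deaths among the unscanned):
- Last scan: scanned non-progressors 0.397 × 0.9 = 0.357; scanned progressors 0.603 × 0.6 = 0.362; estimate 0.630 × 0.357/(0.357 + 0.362) = 0.31.
- Last follow-up: 0.630 × (0.397 + 0.603 × 0.4) = 0.40.

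**Step 5, a harsher scenario by simulation.** 200,000 patients per scenario, median 10 weeks to progression and a further 30 weeks to death, and 10%, 20% or 30% stopping before each scan. Complete scanning gives week-24 PFS of about 19%. Last follow-up gives 28.7%, 37.0% and 44.7%; last assessment gives 18.4%, 17.4% and 16.0%. Stopping accumulates here: 30% before each of three scans leaves 1 − 0.7³ = 66% without the full set. With 0% stopping, the two rules agree at week 24.

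**The case against.** The case for leaving the text alone has real weight.

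- **PFS carries no decision.** It is one of many secondary endpoints in an uncontrolled phase I trial, with no hypothesis, threshold or power. The primary endpoints are adverse events and best response, and the 17 evaluable patients rest on response. This stands, and it limits the importance of the point.
- **Progression may be picked up between scans.** PFS is defined by disease progression, not by scheduled scans alone; disease control is listed at each visit; and patients return to routine oncology care after week 24. So it would be too strong to say that progression cannot be observed. But the article describes no tumour assessment at the visits between scans, and the rule does not depend on one.
- **The figures are assumption-driven.** This stands. The unscanned share is not in the document: the 15% in section 2.11 is a dropout rate, and nothing says those patients remain in contact. The upper end also needs no unscanned patient to die.
- **Operational detail belongs in the full protocol or analysis plan.** That covers missed-scan handling and censoring at new anticancer therapy, which is a choice of estimand and not raised here. It does not cover a censoring date that the article itself states.

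A reader might also infer a PFS plateau lasting up to three years, or OS cut off at week 24. The documents support neither. The plateau requires the telephone calls to count as follow-up, and the OS cut-off requires that they do not; the article does not say which. Section 2.8 limits other endpoints to end of study but sets no such limit on OS.

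**Conclusion.** The rule as written suits OS but not PFS. It biases PFS upward whenever patients stay in contact without being scanned. On a 12-week median and 15% to 30% unscanned after week 8, the excess at week 24 is about 1 to 11 percentage points over a true 25%. The low end has unscanned patients dying at OS medians of 4 to 12 months; the high end has none dying. The harsher scenario in step 5 gives more, and complete scanning gives none to week 24. All these sizes rest on assumed inputs; only the direction follows from the text.

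For scale, if PFS were estimated in the 20 patients at the MTD, the standard error of a 25% rate would be about √(0.25 × 0.75/20) = 0.097, so the excess runs from negligible to about one standard error.

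This is a wording error worth correcting in a descriptive secondary endpoint. It is not a flaw that threatens the trial.

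**What to change.** In section 2.8, replace the PFS censoring sentence with one to this effect: patients without progression or death are censored at the date of their last evaluable tumour assessment without progression, or at first administration of CC-3 if there is no such assessment after baseline. Keep the date last known alive as the censoring date for OS only.

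The cost is one sentence and no new data. Reported PFS may be slightly less favourable. Informative stopping of scans leaves some bias (31% against a true 25% in step 4, compared with 40% under the present rule), so reporting how many patients were in contact but unscanned would help a reader judge what remains.
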